## Abstract

**Introduction:**

Cervical screening rates in the UK are falling, limiting our ability to prevent cervical cancer. Peak incidence of cervical cancer coincides with average age of childbirth, and women with young children are less likely to be screened. Current UK guidelines advise waiting 12 weeks after delivery to perform cervical screening, but this recommendation is not based on evidence from the era of liquid-based cytology or high-risk human papillomavirus (HPV) testing. New mums suggested offering cervical screening at 6 weeks postdelivery, in conjunction with the postnatal check-up with the general practice team in primary care. This study aims to assess the feasibility and acceptability of a paired-sample study design for cervical screening at 6 weeks and 12 weeks postnatal.

**Methods and analysis:**

A study of 100 participants will be performed to assess feasibility and acceptability of cervical screening at both 6 weeks and 12 weeks postnatal, with urine self-sampling using a Colli-pee collection device at each time point. This will inform whether women are prepared to undergo cervical screening at 6 weeks postnatal and the feasibility of a future pair-wise diagnostic test accuracy (of HPV and abnormal cervical cytology) study or whether alternative study designs are needed. Participants must be aged 24.5–64 years old and eligible for the National Health Service Cervical Screening Programme (NHS CSP). At each appointment, participants will complete a questionnaire about their experience and thoughts regarding screening. Substudies ask participants who withdraw or decline to participate their reasons, to identify barriers. The study will be closed for recruitment once 100 participants have completed the 6-week screen in Postnatal Instead of Normally-Timed Cervical Screening (PINCS-1) or if recruitment is poor and 50% not recruited by 6 months, indicating that a paired-sample design is not feasible.

**Ethics and dissemination:**

Ethical approval for PINCS-1 was given by the Stanmore Research Ethics Committee. The results, including participant feedback at each stage, built into the trial design, will inform the design of large studies to determine accuracy and clinical impact of cervical screening at 6 weeks postnatal, identifying whether giving choice (eg, from timing of appointments and/or offering self-sampling) will improve screening uptake. Data will inform the sample size needed for future studies to have adequate power. Results will also inform future NHS CSP management. Results will be shared via scientific publication and via conventional and social media channels accessed by young women.

**Trial registration number:**

ISRCTN10071810.

STRENGTHS AND LIMITATIONS OF THIS STUDYTo our knowledge, this is the first study to focus on acceptability and reliability of cervical screening, including urine self-sampling, in postnatal women, to test hypothesis and generate data to inform further study design, following recommendations by Elridge *et al*.There are multiple points at which acceptability will be assessed by collecting participants’ views and participant-reported outcomes.Data collection tools have been developed using participant responses in the Attitudes to Postnatal Instead of Normally-Timed Cervical Screening (pre-PINCS) study, to ensure applicability to the postnatal population.Pilot diagnostic test accuracy data will inform the sample size calculation for future studies.Screening will be performed in secondary care throughout this study, as this study is designed to test the feasibility of a future paired sample diagnostic test accuracy study, not the effect on uptake in a primary care setting; this is a separate question, requiring a different study design.

## Introduction

 Cervical cancer is one of the most preventable malignancies encountered worldwide, due to a combination of primary prevention (human pHuman Papillomavirus (HPV) vaccination) and secondary prevention (cervical screening) strategies. Global elimination of cervical cancer is a key WHO strategy.^1 2^ By 2022, cervical screening coverage rates in England had fallen to 66% in women/people with a cervix aged 25–49 years, and to less than 50% in some areas. This is markedly below the National Health Service Cervical Screening Programme (NHS CSP) standard of 80%. The majority of cervical cancers now occur in underscreened women.^3^,^5^ Women with young children under 5 years of age are less likely to participate in cervical screening, as are individuals from ethnic minority backgrounds and lower socioeconomic groups, and these groups are also more likely to have had more children and at a younger age.^6^

Peak incidence of cervical cancer in the UK between 2016 and 2019 was in the 30–34 year-old cohort, followed by cases in women aged 25–29 years.^7^ This coincides with the average age of mothers giving birth in England and Wales of 30.9 years.^8^ Our local cervical cancer audit between 2016 and 2017 identified that 15% of women diagnosed with cervical cancer were currently or had recently been pregnant and had been eligible for cervical screening in pregnancy or postnatally, but none had attended. We found that 50% of women were overdue for cervical screening by the end of their pregnancy, and by 6 months postnatal, more than half had still not attended screening.^9^ This quality improvement (QI) project included canvassed views of new mothers/parents and primary care providers, through focus groups, which identified causes of poor uptake and generated ideas for change.^9^ One idea, from both new mothers and primary care practice staff, was to offer postnatal cervical screening at the 6-week postnatal check-up, facilitating easier attendance for women by reducing barriers.^10^ Self-sampling for high-risk HPV (hrHPV) was also suggested to improve screening uptake. Interestingly, offering opportunistic vaginal self-sampling at a General Practitioner (GP)/primary care appointment was demonstrated to be an effective strategy in the recent YouScreen study, potentially leading to a 7.6% improvement in overall screening rates.^11 12^

There are numerous barriers to screening in young women, including a perception that this age group is not at risk, inadequate knowledge, and fear of pain, discomfort and embarrassment. However, being busy and not getting around to having a test were independent factors, regardless of screening status.^13 14^ Our work showed that we could improve uptake by 8% in the postnatal cohort, largely by improving education of midwives and women in pregnancy.^9^ Detailed quantitative and qualitative feedback in the Attitudes to Postnatal Instead of Normally-Timed Cervical Screening (pre-PINCS) acceptability study^15^ (unpublished data) alongside the previous QI project focus groups told us that new parents have many competing priorities and often struggle to address their own health needs.

National Institute for Health and Care Excellence guidelines recommend a 6-week postnatal check for mothers and babies, which is attended by 78% of eligible people.^16 17^ This appointment provides an opportunity for healthcare professionals to discuss multiple topics: infant feeding, lifestyle advice, contraception and health promotion, including discussion of cervical screening.^17 18^ New mothers and primary care staff told us that offering to combine this visit with postnatal cervical screening would remove a significant barrier, particularly as ‘just putting it off’ was the most common reason for younger women being out-of-date for screening in a study by Jo’s Cervical Cancer Trust.^19^

UK national guidance currently advises waiting 12 weeks after childbirth for a routine cervical screening test if it was due in pregnancy.^20^ This recommendation is based on one comparison of conventional cytology with Papanicolaou smear testing at 4 weeks versus 6 weeks versus 8 weeks postnatal in just 55 participants.^21^ There were increased inflammatory changes in Papanicolaou smears taken earlier, leading to more false-positive, low-grade results. However, this predates hrHPV primary testing (or triage) and liquid-based cytology (LBC), which dramatically improve the ability to test even inflammatory samples and those contaminated by blood and lochia.

An Irish observational study, including 556 postnatal women, reported no difference in inadequate cervical sample rates when the cervical sample was taken at 6 weeks postnatal using LBC compared with a non-pregnant gynaecological population consisting of 1429 women.^22^ Using LBC appears to negate the previously held belief that postnatal cervical samples should be delayed until 12 weeks postnatal. HPV testing was not conducted in this study, and there have been no studies directly comparing LBC cervical screening samples at different postnatal time points in a diagnostic test accuracy (DTA) context. Furthermore, hrHPV infection rates are similar during and outside of pregnancy, although these studies performed hrHPV tests at varying postnatal intervals, ranging from 45 days^23^ to 6 months,^24^ and used vaginal swabs rather than clinician-collected LBC samples. This variation limits the applicability of these findings to current UK practice. The current recommendations to delay cervical screening until 12 weeks postpartum are therefore based on long-held perceived wisdom, rather than sound evidence of differences in DTA using current screening methods.

Many women struggle to undergo conventional cervical screening, especially those in higher-risk and socioeconomically disadvantaged groups.^25^ Performing hrHPV testing using self-sampling methods offers an alternative and improves screening uptake in underscreened women.^26 27^ However, previous studies have not specifically targeted postnatal women,^27 28^ whose feelings on vaginal sampling may be affected by recent birth experiences. Our project also provides an opportunity to test the feasibility and acceptability^10^ of self-sampling for hrHPV in urine samples at 6 weeks and 12 weeks postnatal, alongside conventional testing.

We have investigated the acceptability of cervical screening earlier in the postnatal period in a quantitative and qualitative attitudes study (Pre-PINCS – National Institute for Health and Care Research (NIHR) Central Portfolio Management System (CPMS) ID: 55489).^15^ Preliminary analyses suggest that over two-thirds of respondents would be willing to take part in a clinical study of 6 week clinician-taken cervical screening, and nearly 8 out of every 10 would be willing to take part in a study of self-sampling with urine samples (unpublished data).^15^ Over half of the participants agreed or strongly agreed that they would be more likely to have cervical screening if offered at the time of their postnatal check-up (unpublished data). Although this current study is set within the well-established NHS CSP, offering opportunistic cervical screening at the time of the postnatal check-up also offers significant advantages to countries without organised call-recall screening programmes.

### Aim

PINCS is a two-phase study; this protocol refers to PINCS-1, a paired-sample study design comparing postpartum cervical screening performed at 6 weeks or 12 weeks postnatal. The overall aim will be to assess the acceptability and feasibility of this study design in comparing conventional cervical screening and self-sampling at 6 weeks versus 12 weeks postnatal.

### Objectives of PINCS-1

#### Primary objective

To evaluate the feasibility of a paired-sample study design for a future larger scale trial investigating the acceptability of cervical screening at 6 weeks postnatal and willingness to have repeat screening at 12 weeks postnatal.

#### Secondary objectives

To evaluate the acceptability of clinician-taken cervical samples and self-collected urine samples for screening tests in those who decline, and in those who consent both at 6 weeks and 12 weeks using questionnaire data.To assess the quality of cervical samples from clinician-taken samples at 6 weeks postnatal through inadequacy rates.To determine the agreement in hrHPV status at 6 weeks and 12 weeks postnatal between clinician-taken cervical samples and self-collected urine samples.

## Methods and analysis

### Study design

PINCS-1 is a paired feasibility study^29^ to investigate the acceptability of cervical screening and urine self-sampling in postnatal women at 6 weeks and 12 weeks postnatal.

### Study setting

The primary study site will be Somerset NHS Foundation Trust. Two further study sites across South West England will collaborate in this study (Royal Devon and Exeter NHS Trust and Royal Cornwall NHS Foundation Trust), recruiting participants, completing study visits and data collection. Each site is a Gynaecological Cancer Centre. Somerset NHS Foundation Trust acts as the study sponsor. The study planned start date is April 2024 (opened August 2024). Recruitment will end when at least 100 recruited participants have attended and completed clinician-taken cervical screening at their 6-week appointment and have attended or declined to attend their 12-week appointment. If participants withdraw before the 6-week sample, further participants will be recruited, so that at least 100 participants have their 6-week samples performed. The study will end once all participants have completed follow-up, as described above, and data have been collected and analysed. In the instance of low recruitment, an earlier end point may be initiated following discussion with the Independent Trial Steering Committee (ITSC). Anticipated end date is April 2027.

### Patient and public involvement

This study was instigated following the direct request by stakeholders, when investigating methods to reduce barriers to cervical screening in recently pregnant women/people.^9^ Multiple ideas for change were generated through stakeholder groups involving new mothers, young women who had cervical cancer diagnosed shortly after pregnancy and primary care staff directly involved in both postnatal care and cervical screening. In addition to suggestions about improving education about cervical screening for midwives and pregnant women/new parents, both public and healthcare participants identified two areas to target: earlier postnatal screening potentially at the time of the postnatal GP appointment and the use of self-sampling methods.

We worked with local Maternity Voices groups, whose members included women from marginalised communities, to design study materials, questionnaires and semistructured interviews for the pre-PINCS study,^15^ which is currently undergoing analysis. Pre-PINCS was a two-phase study consisting of a questionnaire and indepth qualitative analysis of semistructured interviews. This was performed to gather information, from pregnant women and people within 5 years of their last childbirth, about the acceptability and feasibility of the PINCS studies; these results directly informed the PINCS study design and materials, with specific feedback from participants.

### Participants and recruitment

Potential participants can be identified by members of their existing clinical care team including GPs, community or hospital midwives, health visitors, practice nurses or obstetricians or will be approached if eligible by the local research teams, both antenatally and up to 6 weeks postnatal, in an inpatient or outpatient setting. Potential participants may also self-identify through the publicity literature on recruitment sites and via the social media channels of gynaecological cancer charities (eg, GO Girls, Eve Appeal) and local and national social media groups for new mothers (eg, Mumsnet). Publicity will be in the form of posters and leaflets, distributed via social media, at antenatal events and at routine appointments or shared through the electronic maternity care record. Potential participants will be given a participant information leaflet and, if interested in taking part, they will be referred to a member of the study team. A screening and eligibility questionnaire will be completed with all potential participants and, if eligible and consenting to proceed, an electronic consent form will be completed with an investigator. Participants will be informed of their right to rescind consent at any point during the study and provided with information on how to do this.

Recruitment to PINCS-1 will end when at least 100 recruited participants have attended and completed both clinician-taken cervical sample and urine self-sample at the 6-week appointment and have attended or declined to attend their 12-week appointment. If participants withdraw prior to the 6-week sample, further participants will be recruited. In the instance of low recruitment, an earlier end point may be initiated following discussion with the ITSC. The study will be performed in secondary care, to limit the number of sites required and control for variability of cervical sampling from multiple cervical screeners. This is because this study will examine the feasibility of a future large paired-sample study, comparing DTA of cervical screening at 6 weeks and 12 weeks postnatal. A different study design will be required in a further study to test the effect on uptake of cervical screening, if offered at the 6 week postnatal check-up. This further study will necessarily be conducted in primary care settings. However, we will need to confirm that this is safe and acceptable to the postnatal population before testing within the wider cervical screening programme.

#### Inclusion criteria

Participants aged from 24.5 years (24 years and 183 days or greater on day of consent) to <65 years old.Female with a cervix (regardless of gender identity).Currently pregnant or within 6 weeks of delivery.Able to give informed consent.

#### Exclusion criteria

Absence of a cervix.Not eligible for the NHS CSP.Unable to give fully informed consent.

The study is open to all those eligible for cervical screening, regardless of screening status. To understand the reasons for non-participation and to establish an uptake rate, a cohort of 100 potential participants will be approached and the acceptance rate recorded. All those who decline to participate will be given the opportunity to describe the reasons behind this. All participants who initially gave consent to the study but chose to withdraw it will be offered a short electronic questionnaire to identify any concerns and barriers to participation.

### Sample size

This study will aim to recruit at least 100 participants to the PINCS-1 study. This sample size was chosen following findings from the pre-PINCS study regarding manageable recruitment in postnatal patients as well as input from statisticians and other experienced researchers with experience in feasibility studies.^15^ This sample size will provide a SE on uptake at most 2.5% on each proportion, which we judge to be suitable for assessing acceptability and feasibility of a subsequent paired study design for accuracy. It will inform us as to how prepared women are to undergo cervical screening with a speculum examination at 6 weeks postnatal, and the feasibility of a paired-sample design using repeat testing in the same participant with clinician- and/or self-samples at both or either time points.

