### Statistical analysis

Full details of the statistical analysis will be described in a statistical analysis plan that will be written and finalised before data lock. The primary acceptability outcomes are binary variables; the number of participants attending at 6 weeks of those who consent and the number attending at both 6 weeks and 12 weeks. We will estimate 95% CIs for each using Wilson’s method. The primary feasibility outcome is the recruitment rate in the substudy of 100 consecutive potential participants. We will compare pain scores on a 10-point scale of testing at 6 weeks and 12 weeks, using paired sample analysis and other patient-reported outcome measures. We will compare inadequacy rates of cytology samples at 6 weeks and 12 weeks. We will use 2×2 tables to analyse sensitivity and specificity of: combination HPV testing and cytology of LBC samples at 6 weeks and 12 weeks; HPV testing of LBC samples versus urine samples at both 6 weeks and 12 weeks.

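### The sample size section bounds the standard error of each proportion at 2.5%, but with 100 women the bound is 5%

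*Protocol article*

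**What the plan says.** The Sample size section sets the target: "This study will aim to recruit at least 100 participants to the PINCS-1 study". It says the number came from pre-PINCS experience of manageable recruitment and from advice by statisticians and other researchers. It then gives the resulting precision, "This sample size will provide a SE on uptake at most 2.5% on each proportion", and judges this suitable for assessing acceptability and feasibility. It does not state the proportion at which the figure was calculated.

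The proportions concerned are the primary outcomes in the Statistical analysis section. For acceptability they are "the number of participants attending at 6 weeks of those who consent and the number attending at both 6 weeks and 12 weeks", with the statement "We will estimate 95% CIs for each using Wilson’s method". For feasibility: "The primary feasibility outcome is the recruitment rate in the substudy of 100 consecutive potential participants". The text under Exclusion criteria describes the substudy that is to establish the uptake rate: "a cohort of 100 potential participants will be approached and the acceptance rate recorded". Its denominator is therefore exactly 100.

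The number who consent may exceed 100. Under Study setting, if women withdraw before the 6-week sample, "further participants will be recruited, so that at least 100 participants have their 6-week samples performed".

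**The concern.** An upper limit with no assumed proportion has to hold at every proportion, including 50%, where the binomial standard error is largest. With 100 women that largest value is 5%, so the stated limit looks too small by half.

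This is the only quantitative statement about precision in the section, and the judgement that the sample is adequate is attached to it. It covers the outcomes the study exists to estimate. The Discussion says that uptake and 6-week acceptability will inform whether a definitive trial is justified, and gives a provisional size of over 1000 participants for the accuracy study. Someone relying on the Sample size section would expect these proportions to within about 1.96 × 2.5 = 4.9 percentage points. If the true limit is 5%, the interval is up to twice as wide as that.

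**Working it through.** **Inputs**

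- n = 100: the target in Sample size, and the fixed denominator of the uptake substudy (Exclusion criteria; Statistical analysis).
- Stated maximum standard error: 2.5% (Sample size).
- Assumed proportion: none stated.
- Illustrative proportions. The Introduction reports that in the pre-PINCS survey "over two-thirds of respondents would be willing to take part in a clinical study of 6 week clinician-taken cervical screening", and that nearly 8 in 10 would join a study of urine self-sampling. It also gives 78% attendance at the 6-week postnatal check. The article does not adopt any of these as a design assumption; they only show the range in which results might fall.

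**Attempt to reproduce 2.5%**

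SE = sqrt(p(1−p)/n), with its maximum at p = 0.5:

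sqrt(0.5 × 0.5 / 100) = 0.050, that is 5.0%.

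The stated figure is not reproduced.

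**Standard error and interval by proportion, n = 100**

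| p | SE | Wilson 95% CI | Half-width (points) |
|---|---|---|---|
| 0.50 | 5.0% | 40% to 60% | 9.6 |
| about 0.67 | 4.7% | 57% to 75% | 9.1 |
| 0.80 | 4.0% | 71% to 87% | 7.8 |
| 0.93 | about 2.5% | 86% to 97% | 5.2 |

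At p = 0.78 the SE is 4.1%, and at p = 0.90 it is 3.0%.

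**Where 2.5% would be true with n = 100**

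Solve p(1−p) = 100 × 0.025² = 0.0625. Then p = (1 ± sqrt(1 − 4 × 0.0625))/2 = (1 ± 0.866)/2, so p is 0.067 or 0.933. The SE is 2.5% or less only at or beyond those values.

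**Sample size that would give 2.5%**

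n = p(1−p)/0.025²:

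- p = 0.5: 0.25/0.000625 = 400
- p = 2/3: 0.2222/0.000625 = 356 (rounded up)
- p = 0.8: 0.16/0.000625 = 256

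**Other readings that might rescue the figure**

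1. *Replacement of withdrawals.* If recruitment continues until 100 women have a 6-week sample, about N = 100/p consent, where p is 6-week attendance. Then SE = sqrt(p(1−p)/N) = p × sqrt(1−p)/10. The maximum is at p = 2/3: 0.6667 × 0.5774/10 = 3.85%. At p = 0.8 it is 3.6%, and at p = 0.9 it is 2.8%. It reaches 2.5% or less only for p of about 0.93 or more, or about 0.30 or less.
2. *Pooling the two visits (n = 200).* sqrt(0.25/200) = 3.54%. This would also treat repeated observations on the same women as independent.
3. *Reading 2.5% as a confidence half-width.* The worst-case half-width is 1.96 × 5.0 = 9.8 points, so the gap grows.
4. *Finite population correction.* With a population of 134, 0.05 × sqrt(34/133) = 2.5%. The article gives no such population, and it would not suit inference to a future study.

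None of these gives a maximum of 2.5% from what the article states.

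**The case against.** Four points can fairly be made for the plan.

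- **The number was not derived from the standard error.** The section names manageable recruitment and expert advice as its basis and reports precision afterwards. The early-closure rule in the Abstract (50% not recruited by 6 months) does not use the figure, and no progression threshold in the article depends on it. This stands: it means the sample size itself is not undermined.
- **The results will carry correct uncertainty.** Wilson intervals are planned for the attendance outcomes whatever the Sample size section says. This also stands, and it limits the harm to the planning statement and the judgement attached to it.
- **The survey and postnatal-check figures are not forecasts of this study's outcomes.** Stated willingness and national attendance are poor guides to attendance among women who have already consented, which could be well above 80%. This stands, so those values serve here only as illustrations. The error does not depend on them, because the article claims an upper limit.
- **The factor of two is not uniform.** For 6-week attendance, replacement caps the standard error at 3.85%, about 1.5 times the stated limit. The full 5% applies to the recruitment rate among 100 approached, and can be approached for attendance at both visits.

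The authors may have had a proportion of about 93% or more in mind, but the article does not say so, and an upper limit on each proportion does not fit that reading. Nor can a separate analysis plan make the printed figure true for 100 women.

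**Conclusion.** The statement is wrong as written. With 100 women the standard error of a proportion is at most 5.0%, twice the stated limit in the worst case and 1.6 to 1.9 times it at proportions between 80% and two-thirds. For 6-week attendance with replacement, the excess is at most about 1.5-fold. The 95% interval is about ±8 to 10 points for proportions from 80% down to 50%, not about ±5.

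This rests on simple binomial sampling with independent women and, for the replacement case, on about 100/p women consenting. The error lies in the stated precision and in the suitability judgement made on it. The sample size and the planned Wilson intervals are unaffected. How 2.5% was obtained is not documented.

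**What to change.** Replace the precision sentence in Sample size with wording such as: *With 100 women the standard error of each proportion is at most 5% (95% confidence interval half-width at most about 10 percentage points); for proportions between two-thirds and 80% the half-width is about 8 to 9 points.* Then state again, against that figure, whether the precision is suitable for judging acceptability and feasibility.

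If the authors did intend a high proportion, they should instead state it (about 93% or more), say which outcome it applies to and why it is expected, and drop the claim that the limit holds for every proportion.

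The cost is one sentence and a less favourable precision statement. Neither the sample size nor the analysis needs to change.
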